### Sample size

An a-priori power analysis was conducted to determine the sample size necessary to find statistically significant exercise effects [52]. The sample size calculation is based on the primary outcome and analysis. The sample size was chosen according to the Cohen method, using standard assumptions: 0.05 for significance level, 0.8 for power of test, 0.5 for effect size which accounts, according to Cohen, for medium effect size. For the final analysis, the total participant number will be 156 (39 in each arm). To allow for a 25% dropout rate, 208 senior participants will be recruited.

### Randomization

Randomization will be carried out by stratified sampling using the statistical package R, version 3.2.2. To obtain an equal distribution of senior subjects across the study groups, the allocation will be performed as block randomization. We will use four-in-one blocks. To solve the problem of predicting the next assignment, the allocator will hide the block size from the executer and use randomly mixed block sizes. Randomization order will be determined using a computer-generated random number schedule. Randomization will be performed by a biostatistician not participating in the study. This person will not participate in the conduct of the research, nor will they be involved in the implementation of the exercise programs. The same person will be responsible for ensuring that the participant list remains confidential. Staff performing outcome measurement and data analysis for the primary outcomes will be blinded to group allocation. However, due to the group nature of the care homes, it will not be possible to blind the participants.

### Statistical methods

The basic characteristics of the groups will be established, and the means and medians will be calculated. The confidence intervals for the mean of quantitative variables will also be determined. Percentage distribution and the number of cases will be established for qualitative variables. To check the differences between the groups, an analysis of variance (ANOVA) will be used for normally distributed variables and a Kruskal-Wallis test for non-normally distributed variables. Normality will be assessed with a Shapiro-Wilk test. We will use the Bonferroni correction to appropriately adjust the overall level of significance for multiple comparisons. Alpha levels will be 0.05 and 0.01.

Basic interactions between the studied groups will also be explored. If there is no interaction, we will examine the independent effects of intervention. If there is significant interaction, the values of the coefficients in the multiple regression model will be tested. Interpretation of research results will be based on estimation and associated 95% confidence intervals.

The analysis will be performed on the ITT set. The analysis will be repeated per-protocol (PP) (in which participants who violate the protocol are excluded from the analysis set) and compared to the ITT analysis as a sensitivity analysis. The multiple imputation (MI) technique will used for dealing with missing data under the assumption that data are missing at random [53].

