### Main outcome

The Short Physical Performance Battery (SPPB) is used to evaluate physical fitness [40]. Function of the lower limbs will be assessed using: (1) static balance, (2) gait speed, and (3) getting up from a chair. Each of the elements will be scored from 0 to 4. The final result will be the sum of the points from three attempts.To assess static equilibrium, the participant will perform three stands (side-by-side, semi-tandem, and tandem positions) and hold the position for 10 sTo assess gait, participants will be asked to walk a distance of 3 mTo assess the strength of the lower limbs, the participant will perform the task five times, without using their hands. The total execution time will be recorded

Data will be collected at the following time points: at baseline (before commencement of the intervention), immediately after completion of the intervention, and 12 and 24 weeks after the completion of the intervention.

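### The between-arm comparison of SPPB names no baseline covariate although SPPB is measured at baseline: the test is valid but gives away precision

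*Protocol article*

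**What the plan says.** The Main outcome section makes SPPB, a sum of three components each scored 0 to 4, the primary outcome. On timing it says: "Data will be collected at the following time points: at baseline (before commencement of the intervention), immediately after completion of the intervention", followed by visits 12 and 24 weeks later. The Recruitment section places consent before the baseline assessment, so a baseline SPPB is planned for every participant.

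The Statistical methods section sets the comparison of arms: "To check the differences between the groups, an analysis of variance (ANOVA) will be used for normally distributed variables and a Kruskal-Wallis test" for variables that are not normally distributed, with Shapiro-Wilk deciding between the two. It mentions no analysis of covariance, baseline covariate, change score or model over visits. It then turns to interactions. If there is none, the effects of the interventions are to be examined separately. Otherwise: "If there is significant interaction, the values of the coefficients in the multiple regression model will be tested". The terms of that regression are not listed. Interpretation is to rest on estimates with 95% confidence intervals.

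The Sample size section assumes "0.05 for significance level, 0.8 for power of test" and "0.5 for effect size which accounts, according to Cohen, for medium effect size", and arrives at 156 analysed participants, 39 per arm.

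**The concern.** SPPB before training is likely to predict SPPB after training. A comparison that ignores it leaves that predictable variation in the error term. The covariate costs nothing extra, because the trial already plans to collect it.

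Two features of the plan make this more than a matter of taste. First, SPPB is a bounded integer score, so Shapiro-Wilk could easily reject normality and send the primary outcome to Kruskal-Wallis. That test takes no covariate and does not directly supply the estimates and intervals on which the article says interpretation will rest. Second, the only regression model mentioned depends on a significant interaction. If there is none, no baseline-adjusted analysis is specified.

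Chance imbalance also matters at this size. With 39 per arm, the baseline difference between two arms has a standard error of √(2/39) = 0.23 SD. A gap of at least 0.25 SD, half the target effect, then arises by chance about 27% of the time for any one pair. With equal SDs at the two visits, an unadjusted comparison of follow-up scores carries r times that gap into the estimate.

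**Working it through.** **Inputs from the article.** Alpha 0.05 (taken as two-sided; the article does not say), effect size 0.5 (read as a difference of 0.5 SD), 39 per arm, four equal arms, N = 156.

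**Assumption.** r, the correlation between baseline and follow-up SPPB, is not in the article. It is varied from 0.3 to 0.8. Clustering by home or exercise group is ignored throughout.

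**The plan's own figure.** The dropout allowance reproduces: 156/(1 − 0.25) = 208. The 156 does not reproduce from the stated inputs with the comparisons described. A two-sided t-test of two arms at 0.5 SD needs 64 per arm, a four-group F-test at f = 0.25 needs about 179 in total, and a 2×2 main effect at 0.5 SD needs 128 in total. That mismatch is a separate matter. Here 39 per arm is taken as given.

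**Variance.** Against unadjusted follow-up scores, covariance adjustment leaves residual variance σ²(1 − r²). Against change scores, whose variance is 2σ²(1 − r), the further proportional cut is 1 − (1 − r²)/[2(1 − r)] = (1 − r)/2.

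| r | Cut v. follow-up score (r²) | Equivalent n per arm, 39/(1 − r²) | Further cut v. change score, (1 − r)/2 |
|---|---|---|---|
| 0.3 | 9% | 43 | 35% |
| 0.5 | 25% | 52 | 25% |
| 0.7 | 49% | 76 | 15% |
| 0.8 | 64% | 108 | 10% |

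**Power, like for like.** Each row below keeps the same contrast and changes only the adjustment. The standardised effect becomes 0.5/√(1 − r²).

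- Pairwise: two-sample t-test, 39 v. 39.
- Four-arm omnibus: F-test with 3 numerator df. A 0.5 SD effect of verbal stimulation (two arms high, two low) gives f = 0.25, so the noncentrality is 156 × 0.25² = 9.75, divided by (1 − r²) when adjusted.
- 2×2 main effect: 78 v. 78, 1 df.

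| Contrast | Unadjusted | r = 0.3 | r = 0.5 | r = 0.7 |
|---|---|---|---|---|
| Pairwise | 59% | 63% | 71% | 86% |
| Four-arm omnibus | 74% | 78% | 86% | 96% |
| 2×2 main effect | 87% | 90% | 95% | 99% |

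With Bonferroni for all six pairs, pairwise power is 32% unadjusted, 44% at r = 0.5 and 65% at r = 0.7. The article does not state the number of comparisons, so six is an assumption.

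**The case against.** **The analysed variable is not stated.** The article does not say whether the ANOVA is applied to follow-up scores or to change, and its Objectives speak of the degree of improvement, which could suggest change. This stands as a limit on the size of the gain. If change scores were meant, baseline is already partly used, and the remaining cut is 10% to 25% for r between 0.8 and 0.5. It does not remove the point, because the cut stays positive for any r below 1.

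**Covariate lists are commonly left to the analysis plan.** That is fair for the list of terms in a model. Here, however, the article names the tests themselves, and one of them cannot take a covariate.

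**The gain can be overstated.** A reader might set the 74% of the one-way ANOVA against the 95% of a 2×2 analysis of covariance at r = 0.5 and credit baseline adjustment with the whole 21 points. That changes two things at once. The unadjusted 2×2 main effect already reaches 87%, so about 13 to 14 points come from the single-df contrast and about 7 to 8 from the covariate. For the same reason, baseline adjustment is not the only way to recover power without more residents. The article itself appears to plan the factorial effects when there is no interaction, and at 0.5 SD those exceed 80% without adjustment.

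**Nothing is biased.** A reader might also infer that chance imbalance passes in full into the estimate, or that the planned test is invalid. Neither is supported. Under randomisation the unadjusted estimate is unbiased, and imbalance enters only in proportion to the slope of follow-up on baseline.

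**Conclusion.** The point holds as one of efficiency. The article fixes a comparison of arms that names no use of baseline SPPB, although the trial plans to measure it, and the Kruskal-Wallis branch could not use it.

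The size of the loss depends on a correlation that the article does not give. It is modest at r = 0.3 and substantial from about r = 0.5 upward if follow-up scores are compared, and smaller at high r if change scores are. For the four-arm test, adjustment alone lifts power past the 80% target at r = 0.5 but not at r = 0.3. For a single pair of arms, 71% at r = 0.5 is still short of it. The 2×2 main effects meet the target either way. These figures assume two-sided tests, a true effect of 0.5 SD, 39 analysed per arm and no clustering. The change is worth making, but the plan as written is not invalid.

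**What to change.** Make the primary analysis a linear model of SPPB with baseline SPPB, the two factors (exercise type and verbal stimulation) and their interaction. This may be an analysis of covariance, or a mixed model over the three post-baseline visits. Use it whatever the Shapiro-Wilk result, so that the primary test does not switch to one that cannot adjust. Report adjusted mean differences with 95% confidence intervals. Treat each secondary outcome the same way, with its own baseline as covariate.

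No extra residents, visits or measurements are needed. The cost is a documented change to the analysis wording, made before outcome data are analysed. The Trial status section reports that recruitment was still open when the manuscript was submitted.

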### Interventions

The subjects will be assigned, at random, to one of four groups:Arm 1: basic exercises combined with verbal stimulationArm 2: basic exercises without verbal stimulationArm 3: functional exercise training with verbal stimulationArm 4: functional exercise training without verbal stimulation

Figure 2 shows the overall schedule and time commitment for trial participants.

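### Holm's step-down procedure would be a cheap improvement on the planned Bonferroni correction, which is valid: same family-wise error, more power for second and later rejections

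*Protocol article*

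**What the plan says.** The protocol article (Statistical methods) compares the groups by ANOVA or Kruskal-Wallis and then says: "We will use the Bonferroni correction to appropriately adjust the overall level of significance for multiple comparisons". It adds: "Alpha levels will be 0.05 and 0.01". It does not say how many comparisons the correction covers. The same section first looks for interaction and continues: "If there is no interaction, we will examine the independent effects of intervention". Interpretation is to rest on estimates with 95% confidence intervals, and nothing says that these are simultaneous.

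The four arms cross exercise type (basic or functional) with verbal stimulation (with or without). The Sample size section plans with "0.05 for significance level, 0.8 for power of test, 0.5 for effect size" and arrives at 156 analysed, 39 per arm. It names neither the test nor the number of comparisons behind that figure.

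**The concern.** Bonferroni holds every comparison in a family of m to alpha/m, whatever the other comparisons show. Holm holds the smallest p-value to alpha/m, the next to alpha/(m-1), and so on, stopping at the first failure. Holm's first step is the Bonferroni step, so it cannot reject less. It controls the family-wise error in the strong sense and, like Bonferroni, needs no assumption about how the tests are correlated.

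The design asks two questions: does the type of exercise matter, and does verbal stimulation matter? Under Bonferroni, a real second effect must still meet the stricter level after the first has been established. What is at stake is power for that second finding. Error control and the validity of the results are not in question.

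**Working it through.** **Inputs.** From the article: overall alpha 0.05, power 0.8, effect size 0.5, 39 per arm, 25% dropout. Assumptions, because the article is silent: two-sided tests; effect size read as a standardised mean difference; family of m = 2 (two main effects) up to m = 6 (all pairs of four arms).

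**1. The plan's own figure.** A two-sample t test with d = 0.5 and 80% power gives:

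- at 0.05/2 = 0.025 per test: 77.3, so 78 per factor level; 2 × 78 = 156, or 39 per arm. This matches exactly.
- at an unadjusted 0.05: 63.8, so 64 per level; 2 × 64 = 128. No match.
- a four-arm ANOVA with f = 0.25: about 180. No match.

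Dropout: 156/(1 − 0.25) = 208, as stated. So 156 fits two main effects with Bonferroni already paid for. That reading is inferred, not stated.

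**2. Two main effects, 78 v 78, d = 0.5.** Let b be the power at 0.025 and u the power at 0.05: b = 0.8039, u = 0.8735. The formulas below treat the two tests as independent.

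- Power per factor, Bonferroni: b = 0.804.
- Power per factor, Holm: a factor is rejected if its p ≤ 0.025, or if its p lies between 0.025 and 0.05 and the other p ≤ 0.025. This gives b + (u − b)b = 0.8039 + 0.0696 × 0.8039 = 0.860.
- Both found, Bonferroni: b² = 0.646.
- Both found, Holm: both p ≤ 0.05 and at least one ≤ 0.025. This gives u² − (u − b)² = 2bu − b² = 0.758.
- Only one factor real: the gain is (u − b) × 0.025 = 0.0017, about 0.2 percentage points.

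A simulation of 100,000 trials (39 per arm, pooled variance) agrees:

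| Truth | Quantity | Bonferroni | Holm |
|---|---|---|---|
| Both 0.5 SD | At least one found | 0.960 | 0.960 |
| Both 0.5 SD | Average per factor | 0.804 | 0.860 |
| Both 0.5 SD | Both found | 0.648 | 0.759 |
| One 0.5 SD | Real factor found | 0.804 | 0.805 |
| One 0.5 SD | Family-wise error | 0.024 | 0.044 |
| Neither | Family-wise error | 0.049 | 0.049 |

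Holm uses error rate that Bonferroni leaves unspent, and stays below 0.05.

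**3. Six pairs, 39 per arm.** Each test starts at 0.05/6 = 0.0083. Power for a pair that truly differs by 0.5 SD:

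- both factors active (arm means 0, 0.5, 0.5, 1.0): 0.32–0.33 under Bonferroni, 0.38–0.39 under Holm;
- one factor active: 0.326 and 0.357;
- a single arm differing: 0.326 and 0.346.

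The chance of at least one true rejection changes by no more than 0.0003 (for example 0.654 under both with one factor active). With no true differences, the family-wise error is 0.042 under both.

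In every simulated trial, for both families, Holm's rejections included all of Bonferroni's.

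**The case against.** The strongest reply is that nothing here is wrong. Bonferroni is valid, fixed in advance and strongly controls the error, and the same remark could be made about any trial that uses it. That stands, and it makes this an optional improvement.

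A reader might infer that the trial gives away power for nothing. The documents do not support that, for three reasons.

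- Bonferroni has simple simultaneous intervals that match its tests, and Holm has no equally simple counterpart. In a plan that interprets results through intervals, this counts for something. It is limited, though: the article attaches Bonferroni to the significance level and promises 95% intervals without calling them simultaneous, so nothing promised would be lost.
- The power target is met under Bonferroni. On the reading that reproduces 156, each factor has 80.4% power against the planned 0.8. The article promises no particular power for finding both effects together.
- The larger gains need both factors to be truly 0.5 SD. With one real factor the gain is negligible.

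A reader might also take the six-pair figures as proof that the trial is underpowered. The article does not say that six pairs are the family, and if they were, moving to Holm would not cure the low power.

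One could add that the family, and the choice of procedure within it, belong in an analysis plan that is not shown. That is fair for the family, and its absence is not held against the article. The procedure, however, is named in the article itself.

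**Conclusion.** A cheap improvement, not an error. For testing, Holm is never worse than the stated procedure whatever family is chosen, and the family-wise error stays at or below 5%.

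The size of the benefit is conditional. With the two factors as the family and both truly 0.5 SD, it is 5.6 percentage points per factor (80.4% to 86.0%) and 11.2 for finding both (64.6% to 75.8%). If one factor works, it is about 0.2. With six pairs as the family, it is roughly 2 to 6 points per 0.5 SD pair, from a base of 32–33%. The chance of at least one rejection is unaffected.

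These figures assume two-sided t tests on a roughly normal outcome, no interaction in the two-factor case, 39 analysed per arm, and an overall alpha of 0.05. The dominance of Holm over Bonferroni depends on none of these assumptions.

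**What to change.** In Statistical methods, replace the Bonferroni correction with the Holm step-down procedure and report Holm-adjusted p-values within whatever family is defined. Keep the planned 95% intervals unchanged. Make the change by dated amendment before allocation is revealed to the analysts. The article says that analysts of the primary outcomes are blinded and that recruitment was still open at submission, so a change made without sight of results was feasible then.

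The cost is a few words, with no extra participants or data. The one downside arises if simultaneous intervals are wanted. Bonferroni intervals can be shown beside the Holm p-values, but the two may occasionally disagree. With two comparisons, this happens when the first is significant and the second p-value falls between 0.025 and 0.05: Holm rejects, while the Bonferroni interval includes zero. One sentence saying that the tests follow Holm and the simultaneous intervals follow Bonferroni would deal with that.

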## Discussion

The International Association of Gerontology and Geriatrics-Global Aging Research Network (IAGG-GARN) and the IAGG European Region Clinical Section has developed recommendations for physical activity for older people receiving long-term care [54]. These recommendations stress the importance of motivation and enjoyment as key factors likely to increase the levels of physical activity in this population. In systematic reviews, de Labra et al. [55] and Cadore et al. [56] demonstrated that, despite published evidence of the positive effects of exercise on physical fitness and quality of life in older populations, comparisons of the effectiveness of various exercise programs were necessary. They stated that such an investigation would provide comprehensive information on the impact of regular physical activity on the functional efficiency and stability of older people. As discussed in detail above, here we propose 12 weeks of intervention followed by 6 months of observation, which should demonstrate the impact of an exercise/motivation program on activity and use of free time in a senior population under institutional care.

Mobility and function are important elements of independent living. For residents of care homes, social assistance can help to maintain residents’ physical, psychological and social function, allowing them to maintain control over their own lives. According to Prata et al., functional autonomy increases satisfaction and enhances the quality of life of older people [57]. Weeks et al. found that preventing the aggravation of functional limitations is another important element in motivating older people to participate in exercise [12]. In the planned study, the authors want to determine which form of physical exercise with verbal stimulation will cause improvement in functional performance and changing habitual ways of spending free time among older people. The results of the study will be used to develop a simple, large-scale exercise program for older adults living in institutional care facilities.

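### With 39 per arm, the interaction test that decides which effects are analysed is too weak for a non-significant result to mean there is no interaction

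*Protocol article*

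**What the plan says.** Under Interventions the article states: "The subjects will be assigned, at random, to one of four groups". The arms are basic or functional exercise, each with or without verbal stimulation, which is a 2x2 factorial layout.

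Under Statistical methods the groups are first compared by ANOVA or Kruskal-Wallis, with a Bonferroni correction and alpha levels of 0.05 and 0.01. Interactions are then explored, and two sentences make the next step depend on the result: "If there is no interaction, we will examine the independent effects of intervention" and "If there is significant interaction, the values of the coefficients in the multiple regression model will be tested". The section adds that interpretation will rest on estimates with 95% confidence intervals.

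Under Sample size the calculation is meant to "determine the sample size necessary to find statistically significant exercise effects", with "0.05 for significance level, 0.8 for power of test, 0.5 for effect size" and 39 per arm analysed. No interaction size or interaction power is given. The Discussion says the authors want to "determine which form of physical exercise with verbal stimulation will cause improvement in functional performance".

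**The concern.** Whether verbal stimulation works differently with the two exercise forms is, statistically, the interaction. It is also close to the question posed in the Discussion. The plan makes the choice of analysis depend on a test of that same quantity, in a trial sized for something else. If the test has little power, the first branch will usually be taken even when the benefit sits in one form only. One averaged effect would then be read as applying to both forms. The Discussion says the results will feed a large-scale programme for care homes, so crediting verbal stimulation to the wrong form has practical consequences. A second worry is that choosing between analyses by a significance test need not keep the nominal error rate.

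**Working it through.** **Inputs.** From Sample size: 39 per arm (156 analysed), effect size 0.5, power 0.80, alpha 0.05. From Statistical methods: alpha 0.05 or 0.01, with no statement of which applies to the interaction test. Assumed here: two-sided tests, SD = 1, independent normal data without clustering, and interaction sizes of 0.25 to 1.0 SD.

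**The plan's own figures.** The dropout step reproduces: 156/0.75 = 208. The 39 per arm does not follow from the stated inputs: a two-arm comparison at 0.5 SD needs 63 to 64 per arm, and a 2x2 main effect needs 128 in total. That is a separate matter; 39 per arm is taken as given below. There is no planned interaction power to reproduce.

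**Step 1: precision of the interaction.** It is a difference of two differences, so SE = sqrt(4/39) = 0.320 SD, with 4 × 38 = 152 degrees of freedom. The critical t is 1.976 at 0.05 and 2.609 at 0.01. The 95% interval has half-width 1.976 × 0.320 = 0.63 SD. Even an observed interaction of exactly zero would leave 0.5 SD inside the interval.

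**Step 2: power of the interaction test** (noncentral t; for 0.5 SD the noncentrality is 0.5/0.320 = 1.56).

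| True interaction | alpha 0.05 | alpha 0.01 |
|---|---|---|
| 0.25 SD | 12% | 4% |
| 0.50 SD | 34% | 15% |
| 0.75 SD | 64% | 40% |
| 1.00 SD | 87% | 70% |

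At alpha 0.05, 80% power is reached at about 0.9 SD. For 0.5 SD it would need 4 × (1.960 + 0.842)² / 0.25 = 126 per arm, or 504 analysed.

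**Step 3: the rule when the benefit is in one form only.** Assume verbal stimulation gives 0.5 SD with functional training and 0 with basic exercise. Simulation used 1,000,000 trials, with both stages at 0.05.
- The interaction is missed in 100% − 34% = 66% of trials. The averaged estimate is then (0.5 + 0)/2 = 0.25 SD.
- The main effect also has 34% power here (0.25/sqrt(1/39) = 1.56). The main-effect and interaction contrasts are orthogonal, so the averaged effect is declared after a missed interaction in about 0.66 × 0.34 = 22% of trials. Testing the basic-exercise effect after a significant interaction adds 0.34 × 0.07 = 2%.
- In total a non-existent effect with basic exercise is declared in about 25% of trials, taking a significant averaged effect as a claim for both forms. The real effect with functional training is declared in 53%, against 59% by direct comparison of those two arms.
- With the interaction test at 0.01 these figures become 31% and 43%.

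**Step 4: type I error for verbal stimulation, no effect anywhere.** The main-effect branch at 0.05 contributes 0.95 × 0.05 = 4.75%. The other branch depends on the reading:
- one reference-level coefficient tested: + 0.05 × 0.34, total 6.5%;
- both within-form effects tested at 0.05: + 0.05 × 0.66, total about 8.0%;
- the interaction coefficient itself counted as a finding: + 0.05, total 9.8%;
- both within-form effects at 0.025, main effect left at 0.05: 6.9%;
- 0.025 in both branches: 0.95 × 0.025 + 0.05 × 0.43 = 4.5%;
- interaction test at 0.01, both within-form effects at 0.05: 5.9%.

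**The case against.** The strongest reply is that the rule does not govern the whole analysis. The four-group comparison runs whatever the interaction shows, the interaction work is described as exploratory, and interpretation is to rest on estimates and intervals. This stands in part: a reader might infer that the plan can only ever yield one averaged effect, and the text does not support that. The four-group route is weak protection, however. If Bonferroni covers six pairwise comparisons (0.05/6 each), functional training with against without verbal stimulation has about 32% power for 0.5 SD. Nor is any verbal-stimulation estimate made primary regardless of the interaction result.

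A reader might also infer that the rule seriously inflates type I error, citing 8%, or the roughly 65% chance of a significant within-form effect after a chance-significant interaction. The article does not support that either. The 8% is one reading among several, and Bonferroni at 0.025 in both branches, which the text arguably promises, gives 4.5%. The 65% is conditional on a 5% event and adds only about 3 percentage points overall.

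Third, the 0.5 SD interaction is an assumption. If verbal stimulation helps equally in both forms (0.5 SD), the rule costs almost nothing: 85.5% to 88% power against 87% for the main effect alone.

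Last, the alpha for the interaction test, the coefficients tested and the Bonferroni family may be settled in an analysis plan that is not shown. Their absence is not held against the article. The conditional rule itself is stated, and a plan that followed it would carry it forward.

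**Conclusion.** The concern holds for the power of the interaction test. At 34% power for 0.5 SD (15% at alpha 0.01), non-significance cannot be read as absence of interaction, and the sentence that does so should be changed. In the assumed one-form scenario the cost is an interaction missed in about 66% of trials and a false claim for basic exercise in about 25%. Type I error of roughly 4.5% to 10% makes inflation possible but modest, and it is not the main reason to act.

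It does not follow that averaged main effects must be primary or that the four-arm comparison must go. In the one-form scenario a main effect tested at 0.025 has only 24% power and still estimates 0.25 SD, so that choice alone would not cure the dilution.

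These figures assume two-sided tests, normal independent data and 39 analysed per arm; clustering by care home or exercise group is ignored. The point is worth correcting but does not invalidate the trial.

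**What to change.** Remove the significance condition. Always fit one 2x2 factorial model with exercise type, verbal stimulation and their interaction. Name in advance which verbal-stimulation contrast or contrasts are confirmatory: either the main effect, or the two within-form effects with Bonferroni at 0.025 each. Analyse them whatever the interaction shows. Always report the interaction and both within-form effects with 95% confidence intervals, as estimates and not as a switch between analyses.

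This changes wording only; no participants, visits or data are added. The price is in the choice of contrast. The main effect has SE sqrt(1/39) = 0.160 SD and 87% power for 0.5 SD at 0.05, but it remains an average if an interaction exists. The within-form effects answer the Discussion's question more directly but are less precise: SE sqrt(2/39) = 0.226 SD, with 59% power for 0.5 SD at 0.05 and about 48% at 0.025.
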